#### 2.10.13. Measuring Serum Levels of Various Markers

Various biomarkers have been reported to have different levels in patients with AD, but none has been validated as a definite biomarker [49–51]. In this study we will investigate a number of biomarkers (including IgE) for associations with immunological, inflammatory, psychological, and endocrine factors in AD.

About 4 ml of whole blood will be collected from participants at 3 time points: at baseline; 4 weeks after the completion of acupuncture treatment; and 8 weeks after the follow-up period. Healthy controls will submit to only 1 blood collection (at baseline). Blood will be centrifuged to obtain serum.

Changes in various biomarker levels from baseline to 4 weeks in each of the treatment groups will be examined. Between-group differences will be analysed to explore potential associations with the effect of acupuncture. Analysis of changes from 4 weeks to 8 weeks in group will be conducted to evaluate the sustained effect of acupuncture.

*(1) Serum Total IgE Measurement*. The role of IgE in the pathogenesis of AD is acknowledged as contributing to allergic sensitisation and indirectly supporting AD severity via sensitisation to various allergens [49]. It has been reported that anti-IgE therapy has a curative impact on AD and that it may be an affordable treatment modality [49, 50]. In this study, total IgE levels will be measured using Enzyme Linked Immunosorbent Assay (ELISA).

*(2) Serum Cytokine/Chemokines Measurement*. Based on knowledge of inflammatory mediators and autoimmune responses, a diversity of cytokines have been explored in AD and T cells, and related cytokines are also considered as potential influencing factors in the pathogenesis of AD [52–54]. For instance, overexpression of IL-4 and IL-13 in AD skin was reported and IL-4 was suggested to play a crucial role in AD development [52, 55, 56].

In this context, we will use a commercial kit (Bio-Plex Pro Human Chemokine 40-plex Panel) for the following 40 chemokines from extracted serum samples: 6Ckine/CCL21, BCA-1/CXCL13, CTACK/CCL27, ENA-78/CXCL5, Eotaxin/CCL11, Eotaxin-2/CCL24, Eotaxin-3/CCL26, Fractalkine/CX3CL1, GCP-2/CXCL6, GM-CSF, Gro-*α*/CXCL1, Gro-*β*/CXCL2, I-309/CCL1, IFN-*γ*, IL-1*β*, IL-2, IL-4, IL-6, IL-8/CXCL8, IL-10, IL-16, IP-10/CXCL10, I-TAC/CXCL11, MCP-1/CCL2, MCP-2/CCL8, MCP-3/CCL7, MCP-4/CCL13, MDC/CCL22, MIF, MIG/CXCL9, MIP-1*α*/CCL3, MIP-1*δ*/CCL15, MIP-3*α*/CCL20, MIP-3*β*/CCL19, MPIF-1/CCL23, SCYB16/CXCL16, SDF-1*α*+*β*/CXCL12, TARC/CCL17, TECK/CCL25, and TNF-*α*.

*(3) Serum Cortisol Measurement*. Cortisol, also called glucocorticoid, is a well-known stress-related hormone associated with the hypothalamic-pituitary-adrenal (HPA) axis and its mechanisms have been elucidated by analysing physiological change in stress response systems on a variety of psychological issues [57–60]. In this study, serum cortisol level will be used to assess HPA function in accordance with the stress response of participants. Total cortisol levels will be measured using ELISA.

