#### 2.10.14. Exploring Biomarkers with MicroRNA Expression Profiling

AD is known as a complex genetic skin disease affected by environmental distress and resulting from abnormal immune responses as well as malfunctions of the skin barrier [50, 61]. But no specific biomarker for the diagnosis of atopic disorder has yet been identified [50, 51]. In this context, microRNA (miRNA) will be analysed in order to explore new candidates associated with the development of AD and its treatment with acupuncture.

A miRNA is a small noncoding RNA molecule. Since its function is related to eukaryotic cells, dysregulation of several specific miRNAs has been reported to be associated with several pathological processes, such as chronic lymphocytic leukemia and cardiomyopathy [62, 63]. In the study of AD, some miRNAs were proposed to be related to AD symptoms [64, 65], but none has been confirmed as a predictive or prognostic marker.

Illumina sequencing using serum will be performed for miRNA expression profiling to determine candidate miRNA biomarkers for the effectiveness of acupuncture. The difference between participants with AD and healthy controls at baseline will be analysed to explore potential biomarkers associated with the development of AD. Within the pool of biomarker candidates related to AD, the difference between VA1 or VA2 (whichever is more efficacious) and SA at 4 weeks will be compared, to determine biomarkers related to acupuncture effect. The difference between VA and SA at 8 weeks will also be analysed to examine whether the selected biomarkers at 4 weeks continue to be significant at 8 weeks, to explore sustained effects of acupuncture (Figure 2).

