### 2.11. Statistical Methods

#### 2.11.1. Sample Size Calculation

The proposed study is a RCT whose primary aim is to investigate the feasibility to recruit and treat participants with AD with acupuncture and to evaluate acupuncture's antipruritic effects. We will calculate the effect sizes of key outcomes including itch VAS and SCORAD index, to inform power calculations for a further large-scale study. A total of 30 individuals with AD and 20 healthy controls will be recruited during the study period; participants with AD will be randomly assigned in a 1 : 1 : 1 ratio to one of two active acupuncture regimens or sham acupuncture. Healthy controls will not receive any treatment. Considering an estimated 20% dropout rate, we identified the sample size with the advice of a statistician. The statistical significance level will be set at 0.1 considering the applied small size.

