#### 2.11.2. Statistical Analysis Plan

We will perform descriptive analyses for all outcome measures. Categorical variables will be provided with percentages, and continuous variables will be provided as means with standard deviations. An independent statistician will perform statistical analyses using SPSS 21.0 (IBM SPSS Statistics, New York, USA). Missing data will be replaced by carrying forward the most recent nonmissing value, and the time and reason for the missing data will be recorded. Depending on the recorded reasons, multiple imputation by an independent statistician will be done and compared.

The effectiveness of the intervention will be provided by examining changes in outcome measures between baseline and end of treatment and through the follow-up period, using a repeated measures analysis of variance (ANOVA) and *χ*^2^ test. The difference in effect between VA1 and VA2 will be analysed by examining changes in the itch VAS and SCORAD index, by the Mann–Whitney *U* test on continuous variables and *χ*^2^ test on categorical variables. The difference in therapeutic effect between VA (using the most efficacious dose between VA1 and VA2) and SA will be investigated in the same way. The data will be analysed with a *p* = 0.1 (two-sided) statistical significance level and 90% confidence intervals will be provided following the statistician's advice for a small sample size. The current data will be used to calculate the number of participants needed to reach a significance level of 0.05 and 80% power.

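### The sustained effect on serum markers is evaluated by an uncontrolled within-group change from week 4 to week 8; it should be evaluated against sham at week 8

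*Protocol article*

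**What the plan says.** Section 2.10.13 of the protocol article gives three analyses for the serum markers, in this order:

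1. "Changes in various biomarker levels from baseline to 4 weeks in each of the treatment groups will be examined".
2. "Between-group differences will be analysed to explore potential associations with the effect of acupuncture". This sentence names no time window.
3. "Analysis of changes from 4 weeks to 8 weeks in group will be conducted to evaluate the sustained effect of acupuncture".

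Section 2.10.14, on microRNA, takes up the same question with a different analysis: "The difference between VA and SA at 8 weeks will also be analysed". Its stated purpose is also to explore sustained effects.

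Section 2.11.2 adds a general repeated measures ANOVA of the outcome measures, running through follow-up, and sets the error level: "The data will be analysed with a *p* = 0.1 (two-sided) statistical significance level and 90% confidence intervals will be provided". On size, section 2.11.1 says: "A total of 30 individuals with AD and 20 healthy controls will be recruited during the study period". The patients are randomised 1:1:1. Table 2 schedules blood at baseline, week 4 and week 8 for all patients with atopic dermatitis, including the sham arm. Healthy controls give blood once, at baseline.

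**The concern.** The third sentence names both the question (does the effect of acupuncture last?) and the method (change from week 4 to week 8 inside a group). The method does not answer the question.

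An effect of acupuncture is a difference from what would have happened without it, and in this trial only the sham arm shows that. Between week 4 and week 8 a marker can move because the disease relapses and remits, as the Background section describes. It can also move because of rescue topical steroid, which section 2.10.6 permits and which is still recorded at the week 6 telephone interview and the week 8 visit. Healthy controls cannot separate these influences, since they have no second sample.

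At stake is what the trial reports on persistence for 42 markers (1 + 40 + 1), under its third stated aim. The statement would not rest on the randomised comparison, although the data for that comparison will exist.

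**Working it through.** **The plan's own figure.** The 30 patients cannot be derived, because section 2.11.1 gives no effect size, SD or power. It says only: "Considering an estimated 20% dropout rate, we identified the sample size with the advice of a statistician". The figure is compatible with 8 evaluable patients per arm: 8 / (1 − 0.20) = 10 per arm, and 3 × 10 = 30. I therefore use n = 10 (no loss) and n = 8 (20% loss).

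**What the within-arm change can show.** Write the verum change from week 4 to week 8 as D + E, where D is the drift that would occur anyway and E is the change in the acupuncture effect. The sham change is D, if sham itself has no effect on the marker. The within-arm analysis estimates D + E; the question concerns E.

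- *No effect at any time, stable marker* (D = 0, E = 0): a two-sided test at 0.10 finds no change in 1 − 0.10 = 90% of cases. There was no effect to sustain, yet the result looks the same as a kept effect.
- *Effect fully kept, both arms drift* (E = 0, D = 0.5 SD of the paired change): the within-arm test signals a change in 36% (n = 8) or 43% (n = 10) of cases, suggesting loss. A test of the verum-sham difference in change rejects at its nominal 10%.

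**How often a real loss would go undetected.** For a paired t-test at two-sided 0.10, with true loss δ in SDs of the paired change:

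power = 1 − F(t; n − 1, δ√n) + F(−t; n − 1, δ√n)

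Here F is the noncentral t distribution function and t its central 95% point (1.895 for n = 8, 1.833 for n = 10). At δ = 0.5 the noncentrality is 0.5 × √8 = 1.41 or 0.5 × √10 = 1.58. The values of δ are assumptions.

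| δ (assumed) | missed, n = 8 | missed, n = 10 |
|---|---|---|
| 0.3 | 0.802 | 0.773 |
| 0.5 | 0.642 | 0.572 |
| 0.8 | 0.347 | 0.246 |
| 1.0 | 0.185 | 0.102 |

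The 90% CI half-width for the paired change is 1.895/√8 = 0.67 SD or 1.833/√10 = 0.58 SD. The calculation takes observed pairs only and leaves out the carrying forward of missing values described in section 2.11.2.

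**The alternative, on the same terms.** For verum minus sham at week 8, without baseline adjustment and in SDs of the marker level, the 90% CI half-width is t × √(2/n): 1.761 × √(2/8) = 0.88 SD or 1.734 × √(2/10) = 0.78 SD. With noncentrality d√(n/2), power for a 0.5 SD difference is 25% (n = 8) or 29% (n = 10), and for 0.8 SD it is 45% or 53%. These SDs are on a different scale from those in the table, so the two sets are not directly comparable. Baseline adjustment narrows the interval to the extent that baseline predicts week 8; the document gives no correlation from which to say how far.

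**The case against.** The strongest reply is that the plan commits to less than a critic may read into it.

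- *A reader might infer that the plan treats a non-significant change as persistence.* It does not say so. Section 2.10.13 states no threshold and no decision rule, and section 2.11.2 promises 90% confidence intervals. This objection stands: the miss rates above apply only if little or no detected change is read as durability.
- *A reader might infer that a week 8 comparison with sham is planned for microRNA alone.* That is too absolute. The between-group sentence in section 2.10.13 has no time limit, and the ANOVA in section 2.11.2 could include a group-by-time comparison through week 8. But neither explicitly ties a week 8 verum-sham contrast to the sustained effect on serum markers, whereas the sentence that does address it points inside the group.
- *A reader might add regression to the mean.* The documents do not support it here. Entry selection is on itch VAS and SCORAD at enrolment, not on serum markers or on week 4 values.
- *The remedy has low power too.* True, as the figures show. The microRNA section is also no complete model: it asks whether markers remain significant and uses whichever verum arm looks more efficacious.
- *The study is exploratory, with feasibility as its primary aim.* Also true. It limits the weight of the point but does not make the within-arm change an answer to the question.

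**Conclusion.** The point holds as a mismatch between question and analysis. For 42 serum markers, the only analysis explicitly assigned to the sustained effect has no control, while the adjoining section uses the sham arm for the same question. This is a stated choice and not a detail left to another document.

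Its size depends on how the result is read. If absence of a detected change were taken as persistence, a true loss would be missed in 77-80% of cases at 0.3 SD, 57-64% at 0.5 SD, 25-35% at 0.8 SD and 10-19% at 1.0 SD of the paired change. This assumes 10 to 8 patients per arm, two-sided alpha 0.10, and a t-test on approximately normal changes. The stronger statement, that the plan will call a rebound sustained in 57-64% of arms, is not supported: it needs a decision rule that the protocol does not contain and one particular assumed effect size.

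The consequence is a possibly mislabelled exploratory conclusion. No sample size or confirmatory claim depends on it. The gain from changing the analysis is validity, not precision.

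**What to change.** Replace the last of the three analysis sentences in section 2.10.13 with wording such as:

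> The sustained effect on serum markers will be estimated as the difference of each verum arm from sham at week 8, adjusted for the baseline level, and reported with a 90% confidence interval. Within-arm changes between weeks 4 and 8 will be presented descriptively.

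Naming each verum arm avoids choosing the better-looking one first. Reporting an estimate and interval, not a significance verdict, matters because either analysis is weak at this size.

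The cost is one sentence. No extra visit, sample or assay is needed, since week 8 blood is already scheduled in all three arms. The drawback is a wide interval, with a half-width of about 0.78 to 0.88 SD before baseline adjustment, so conclusions on persistence stay exploratory.

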#### 2.10.14. Exploring Biomarkers with MicroRNA Expression Profiling

AD is known as a complex genetic skin disease affected by environmental distress and resulting from abnormal immune responses as well as malfunctions of the skin barrier [50, 61]. But no specific biomarker for the diagnosis of atopic disorder has yet been identified [50, 51]. In this context, microRNA (miRNA) will be analysed in order to explore new candidates associated with the development of AD and its treatment with acupuncture.

A miRNA is a small noncoding RNA molecule. Since its function is related to eukaryotic cells, dysregulation of several specific miRNAs has been reported to be associated with several pathological processes, such as chronic lymphocytic leukemia and cardiomyopathy [62, 63]. In the study of AD, some miRNAs were proposed to be related to AD symptoms [64, 65], but none has been confirmed as a predictive or prognostic marker.

Illumina sequencing using serum will be performed for miRNA expression profiling to determine candidate miRNA biomarkers for the effectiveness of acupuncture. The difference between participants with AD and healthy controls at baseline will be analysed to explore potential biomarkers associated with the development of AD. Within the pool of biomarker candidates related to AD, the difference between VA1 or VA2 (whichever is more efficacious) and SA at 4 weeks will be compared, to determine biomarkers related to acupuncture effect. The difference between VA and SA at 8 weeks will also be analysed to examine whether the selected biomarkers at 4 weeks continue to be significant at 8 weeks, to explore sustained effects of acupuncture (Figure 2).

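### MicroRNA candidates are picked by successive significance filters and the only threshold stated is two-sided p = 0.1, so chance candidates are expected; the contrast with healthy controls is also open to confounding

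*Protocol article*

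**What the plan says.** **MicroRNA (protocol article, section 2.10.14).** Serum is sequenced. Patients with AD are compared with healthy controls at baseline to form a pool. The next step is "Within the pool of biomarker candidates related to AD, the difference between VA1 or VA2 (whichever is more efficacious) and SA at 4 weeks". The week-8 comparison is then made "to examine whether the selected biomarkers at 4 weeks continue to be significant at 8 weeks", and this is read as evidence on sustained effect.

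**Serum markers (section 2.10.13).** "we will use a commercial kit (Bio-Plex Pro Human Chemokine 40-plex Panel) for the following 40 chemokines from extracted serum samples". Total IgE and cortisol are added. These markers are examined as changes from baseline to 4 weeks, with between-group differences, and from 4 to 8 weeks. No rule for naming a serum marker as a candidate is stated.

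**Threshold.** Section 2.11.1: "The statistical significance level will be set at 0.1 considering the applied small size". Section 2.11.2: "The data will be analysed with a *p* = 0.1 (two-sided) statistical significance level and 90% confidence intervals will be provided". The article gives no other threshold.

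**Patients and controls (sections 2.4.1 and 2.4.2).** Controls must have no present or past allergic disease, rhinitis included. They must not be pregnant or lactating, and must not have used antihistamines or steroids regularly in the previous month. Patients must be off prescription AD drugs for a month. Patients with asthma or bronchitis, disallowed treatments such as oral corticosteroids, or other disorders that could affect the outcomes are excluded. The patient criteria do not mention rhinitis, pregnancy or lactation, or antihistamines by name.

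**The concern.** Biomarker discovery is the third aim of the trial (section 2.1). A small sample is a reason to expect low power. It is not a reason to loosen the threshold when many markers are screened at once, because the number of chance hits grows with the number of tests and with alpha.

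Three features of the microRNA route add to this.

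- The week-8 check uses the same patients as the week-4 selection, so it is not independent support.
- The verum–sham contrast is stated as a difference at 4 weeks, with no baseline term, although every patient gives a baseline sample.
- The pool is defined by a non-randomised comparison with healthy volunteers selected under different rules. The differences found are to be linked to how AD develops.

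At stake is follow-on work built on candidates whose expected error rate the reader cannot judge.

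**Working it through.** **Inputs from the article.** 30 patients in three arms give 10 per arm. With the stated 20% dropout, 10 × 0.8 = 8 per arm. There are 20 healthy controls. Alpha is 0.1, two-sided. The printed analyte list counts to 40, matching the stated panel size; with IgE and cortisol the total is 42. The sample size has no effect size, SD or power behind it, so it cannot be derived for the biomarkers.

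**Assumptions (not in the article).** 200 to 1,000 microRNAs tested; standardised effects d = 0.5 to 1.0; 10% or 20% of markers truly related; correlation rho between weeks 4 and 8 of 0.5 to 0.8.

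**1. MicroRNA, nothing real.**
- Pass AD versus healthy: m × 0.1 = 200 × 0.1 = 20, up to 1,000 × 0.1 = 100.
- Also pass verum versus sham: m × 0.1 × 0.1 = 2, up to 10.
- Chance of at least one, if markers are independent: 1 − 0.99^200 = 86.6%, and above 99.9% for 1,000.

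The multiplication is fair. With equal arms the verum–sham difference is uncorrelated with the overall AD mean. A null simulation with a baseline to week-4 correlation of 0.7 gave 0.00997 for passing both steps.

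**2. True AD markers that acupuncture leaves unchanged.** They enter the pool legitimately, so the first filter gives no protection. Each passes verum versus sham with probability 0.1.

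**3. Serum markers, if the same threshold is used to name them.** 42 × 0.1 = 4.2 expected false positives per contrast when nothing is real. This expectation holds whatever the correlation between markers. The chance of at least one is 1 − 0.9^42 = 98.8%, but only under independence, which is doubtful for related chemokines.

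**4. Share of verum–sham hits that are false.** With f the share of markers truly related, the formula is 0.1(1 − f) / [0.1(1 − f) + power × f]. At 10 per arm, power from the noncentral t is 0.288 for d = 0.5 and 0.694 for d = 1.0.

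| n per arm | f | d = 0.5 | d = 1.0 |
|---|---|---|---|
| 10 | 10% | 0.09/(0.09 + 0.0288) = 75.8% | 0.09/(0.09 + 0.0694) = 56.5% |
| 10 | 20% | 58.1% | 36.6% |
| 8 | 10% | 78.3% | 59.9% |

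Most hits are false when f is below 0.1/(0.1 + power). At 10 per arm that is 25.8% for d = 0.5 and 12.6% for d = 1.0.

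**5. Week 8 as confirmation.** By simulation under the null at 10 per arm, a false week-4 hit is significant again in the same direction 23% of the time at rho = 0.5 and 48% at rho = 0.8. Independent data would give 0.1/2 = 5%.

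**6. Baseline term.** Relative to a week-4-only comparison, baseline adjustment multiplies the variance by 1 − rho², where rho is here the correlation between baseline and week 4. This is 0.75 at rho = 0.5 and 0.51 at rho = 0.7.

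**7. AD versus healthy.** With 30 against 20, a marker shifted by 0.3 SD through a confounder alone passes at p < 0.1 with probability 27%, against 10% for a null marker.

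**The case against.** The strongest reply is that this is a small feasibility study. The biomarker work is called exploratory, its results are called candidates, and an article condenses a fuller protocol in which error control and covariates may be set out. That stands in part: the silence on multiplicity is not itself the finding. What remains is what is written, namely significance as the filter and 0.1 as the only threshold, justified by small size. Section 2.11.2 reaches that threshold after discussing clinical outcomes, so applying it to the sequencing is an inference. It is a fair one, since the sentence covers the data in general and no other level appears.

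Several stronger readings are tempting, and the documents do not support them.

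- *Most named biomarkers will be chance.* This needs a low share of true markers. At 20% true and d = 1.0 the false share is 36.6%.
- *The serum markers ignore baseline.* They do not: section 2.10.13 analyses change from baseline and states no selection step.
- *The missing baseline term confounds the microRNA contrast.* Verum versus sham is randomised, so the false-positive rate stays at 0.1. The loss is precision, and chance imbalance is left uncorrected at 8 to 10 per arm.
- *Patients were barely screened.* Section 2.4.1 also excludes disallowed treatments and other disorders that could affect outcomes. The mismatch is confined to items not named for patients, and the rule on prescription drugs may cover some antihistamine use.
- *Using the better verum arm inflates error here.* In simulation the null type I error stayed between 0.097 and 0.103.
- *The sequencing tests every known microRNA.* The article gives no number.

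**Conclusion.** The concern holds in a limited form. Followed as written, the microRNA route is expected to yield 2 to 10 chance candidates after two filters if 200 to 1,000 are tested and none is real. In addition, 10% of the true AD markers that acupuncture does not affect would pass verum versus sham. Repeat significance at week 8 adds little. The figure of 4.2 false positives for the 42 serum markers applies only if the 0.1 level is used to name them.

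The false share of hits is 56.5% to 75.8% at 10 per arm if 10% of markers are real and d lies between 1.0 and 0.5. It is therefore possible, but not shown, that most are chance.

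Confounding is a concern for the AD–healthy contrast alone. Differences there may reflect rhinitis, pregnancy or lactation, antihistamine use, age or sex. The missing microRNA baseline term is a matter of efficiency and chance imbalance. The plan should be changed, but the clinical comparisons are not affected.

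**What to change.** Revise the analysis wording in sections 2.10.13, 2.10.14 and 2.11.2 as follows.

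1. Within each biomarker contrast, report Benjamini-Hochberg q-values and the number of markers tested. Name candidates at a 10% false discovery rate. Present the rest as ranked estimates with intervals, labelled descriptive.
2. Adjust week-4 and week-8 microRNA for the patient's own baseline value.
3. Adjust AD versus healthy for age and sex; Table 2 collects demographics on everyone. Add a sensitivity analysis that drops patients who meet a healthy-control exclusion, where the medical history records it.
4. Describe week 8 as the course of the selected markers over time, not as confirmation.

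No new samples or visits are needed. The cost is fewer named candidates, possibly none, at 8 to 10 patients per arm; the ranked estimates would still inform a later study.

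### Persistence of microRNA effects is judged by whether week-4 markers are still significant at week 8, a criterion that tends to understate persistence at 8 to 10 patients per arm

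*Protocol article*

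**What the plan says.** Section 2.10.14 describes a sequence of steps. Candidate microRNAs related to atopic dermatitis are first identified by comparing patients with healthy controls at baseline. Within that pool, "the difference between VA1 or VA2 (whichever is more efficacious) and SA at 4 weeks will be compared, to determine biomarkers related to acupuncture effect". For week 8 the section adds: "The difference between VA and SA at 8 weeks will also be analysed", with the purpose to "examine whether the selected biomarkers at 4 weeks continue to be significant at 8 weeks, to explore sustained effects of acupuncture". This is the only persistence criterion the article states for microRNA.

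The sample size is in section 2.11.1: "A total of 30 individuals with AD and 20 healthy controls will be recruited during the study period", with patients "randomly assigned in a 1 : 1 : 1 ratio to one of two active acupuncture regimens or sham acupuncture". The same section adds: "Considering an estimated 20% dropout rate, we identified the sample size with the advice of a statistician". Section 2.11.2 sets the error level: "The data will be analysed with a *p* = 0.1 (two-sided) statistical significance level and 90% confidence intervals will be provided". It names the Mann–Whitney test for continuous variables in the VA1–VA2 comparison and applies the same approach to VA against SA. It also plans last observation carried forward (LOCF), with multiple imputation as a comparison depending on the reason for missingness.

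Two other provisions touch on time course. Section 2.10.13 plans an analysis of change from week 4 to week 8, but within group and for the other serum markers. Section 2.11.2 plans a repeated measures ANOVA through follow-up for outcome measures in general.

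**The concern.** The criterion asks whether a significance label is repeated, which is a different question from whether the difference was maintained. A difference can be unchanged and still miss the threshold at a second look, because power at 8 to 10 per arm is modest. Selection adds to this. Markers reach the week-8 look only because their week-4 difference was large enough to be significant, so on average that difference is overestimated. Some will fall below the threshold at week 8 by regression to the mean, with no change in the true effect.

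Discovering biomarkers of the acupuncture effect is the third stated aim (section 2.1), and section 2.10.14 uses the week-8 look to explore durability. At stake is how candidate markers are described. A list of markers that did or did not remain significant would make the effect look less durable than it may be.

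**Working it through.** **Inputs from the article.** 30 patients, 1:1:1, so 30/3 = 10 per arm; with 20% dropout 10 × 0.8 = 8 per arm. Two-sided level 0.1.

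**Plan's own figure.** The article gives no effect size, SD or power for the microRNA comparison, so there is no power figure to reproduce. The only possible check is 8/(1 − 0.2) = 10, which is consistent, but the 8 is itself inferred from the dropout rate.

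**Assumed, not in the article.** True standardised difference d = 0.5, 0.8, 1.0 or 1.5 SD, identical at both weeks; within-patient correlation ρ = 0.3 to 0.7; normal data. Not modelled: choosing the better VA arm, preselecting the disease-related pool, and any multiplicity control across microRNAs.

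**Step 1: threshold.** The observed difference needed for significance is t(0.95; 2n − 2) × √(2/n).
- n = 10: 1.734 × 0.447 = 0.78 SD.
- n = 8: 1.761 × 0.500 = 0.88 SD.

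**Step 2: power of one comparison** (noncentral t, noncentrality d√(n/2)).

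| d | 0.5 | 0.8 | 1.0 | 1.5 |
|---|---|---|---|---|
| n = 10 | 29% | 53% | 69% | 94% |
| n = 8 | 25% | 45% | 60% | 89% |

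**Step 3: selection effect.** By simulation with n = 10 and d = 0.8, markers significant at week 4 show a mean week-4 difference of 1.12 SD. With no true change, the expected week-8 difference is d + ρ(1.12 − d):
- ρ = 0.3: 0.8 + 0.3 × 0.32 = 0.90 SD.
- ρ = 0.7: 0.8 + 0.7 × 0.32 = 1.02 SD.

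So an apparent decline of 0.22 to 0.10 SD arises from selection alone.

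**Step 4: P(not significant at week 8 | significant at week 4), constant true difference.** The t-test figures are simulated, counting significance in the same direction. Repeated runs agree to about one percentage point. Each range runs from ρ = 0.7 to ρ = 0.3.

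| d | t-test, n = 10 | t-test, n = 8 | Mann–Whitney, n = 8 |
|---|---|---|---|
| 0.5 | 39–60% | 42–63% | 46–68% |
| 0.8 | 25–38% | 29–45% | 35–51% |
| 1.0 | 16–25% | 21–33% | 26–38% |
| 1.5 | 4–5% | 7–10% | 10–14% |

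Mann–Whitney with n = 10 also gives somewhat higher rates than the t-test: 28–43% at 0.8 SD, 20–29% at 1.0 SD and 5–7% at 1.5 SD.

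**Step 5: factors that lower the rate.**
- Higher correlation: at ρ = 0.9, d = 0.8, n = 10, the t-test rate is 14%.
- LOCF: if 2 of 10 patients in each arm have week-4 values copied into week 8, the t-test rate at d = 0.8 falls from about 38% to 34% (ρ = 0.3) and from about 24% to 22% (ρ = 0.7). This is artificial persistence, because a copied value carries no information about week 8.

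**Step 6: precision of a direct comparison.** The 90% half-width for the change in the VA−SA difference is t × √(4(1 − ρ)/n). At ρ = 0.5:
- n = 10: 1.734 × √0.200 = 0.78 SD.
- n = 8: 1.761 × √0.250 = 0.88 SD.

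With a constant true difference, a test of this change at 0.1 rejects in about 10% of runs whatever d is. Non-rejection would not prove persistence.

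**The case against.** A reader might infer that markers losing significance will be dropped as candidates or labelled transient. The article does not say so. Candidates are determined at week 4, the week-8 look is additional, and no deselection rule or classification is stated. That reading should not be attributed to the plan.

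A reader might also infer that the trial has no interval estimate or time-course analysis that could help. That goes too far as well. Section 2.11.2 states that "90% confidence intervals will be provided following the statistician's advice for a small sample size" and plans a repeated measures ANOVA through follow-up; both may be meant to cover microRNA. Neither is tied to the persistence question, however, and section 2.10.14 names significance as what is examined. Because that criterion is written down, this is not merely a detail left to a fuller plan.

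Further objections stand in part. The study is exploratory, and section 2.10 declines to rank outcomes for that reason, so no confirmatory claim or sample-size input depends on this look. The size of the problem depends on assumed effect sizes as well as assumed correlations. The largest rates belong to 0.5 SD, where only about 29% of markers would pass week 4 at all, and at 1.5 SD the problem nearly disappears. The remedy is itself imprecise and sets no persistence margin. These arguments make the point minor; they do not make repeated significance a sound measure of persistence.

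**Conclusion.** The point holds as a minor one about a stated criterion and its interpretation. Repeated significance at week 8 is a poor indicator of a sustained microRNA effect in a comparison of 8 to 10 patients per arm, and failing it does not show that the difference shrank. For a truly constant difference of 0.5 to 1.0 SD, between about one in six and three in five markers significant at week 4 would be non-significant at week 8 (16–60%, t-test, 10 per arm, ρ = 0.7 to 0.3). At 1.5 SD the figure is 4–5%. Rates are somewhat higher with Mann–Whitney or 8 per arm, and lower with higher correlation or where LOCF copies week-4 values forward. All of these rest on effect sizes and correlations that the article does not supply. The supported conclusion is that the only stated microRNA persistence criterion would tend to understate persistence, not that the investigators will discard markers.

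**What to change.** Replace the week-8 sentence in section 2.10.14 with wording such as: *For each microRNA carried forward from week 4, the VA−SA difference at week 8 and the change in that difference from week 4 to week 8 (arm-by-time contrast) will be reported with 90% confidence intervals, using observed and not carried-forward week-8 values. Loss of significance at week 8 alone will not be interpreted as loss of effect.*

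The cost is one extra contrast per selected marker on samples already due to be sequenced, at a confidence level already planned. The downside should be stated with the results. The contrast is imprecise (half-width about 0.8 to 0.9 SD at ρ = 0.5), and selection on week 4 biases it towards apparent decline. Many markers will have to be reported as persistence undetermined.
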